## Abstract

**Background:**

African Americans suffer disproportionately from tobacco-related illness and have more difficulty quitting smoking than other racial/ethnic groups. Previous research indicates that African American treatment-seekers are high utilizers of tobacco quitlines, yet cessation rates via quitlines are lower relative to whites. The goal of the present study is to test the effectiveness of adding a culturally specific, video-based, adjunct to standard quitline care. It is hypothesized that the integration of an evidence-based intervention (*Pathways to Freedom: Leading the Way to a Smoke-Free Community©; PTF*) into quitline services will increase cessation and treatment engagement compared to control conditions, and that effects will be moderated by sociocultural factors (e.g., culturally specific intervention expectancies, acculturation, and ethnic identity).

**Methods:**

This study is a 3-arm semi-pragmatic randomized controlled trial (RCT). Participants will be 1050 enrollees in the North Carolina State quitline (QuitlineNC) who self-identify as African American. Usual quitline care includes up to 4 proactive quit coaching calls, website access, and two-weeks of nicotine patch therapy. Eligible study participants will be randomized to receive (1) standard quitline services plus *PTF (PTF)*; (2) quitline services plus a standard tobacco cessation DVD (attention control); or (3) quitline services alone (usual care). Assessments will be conducted at baseline, 3 and 6-months post-enrollment. The primary outcome will be biochemically verified 7 day ppa at 6-months. Generalized linear mixed models (GLMMs) and hierarchical logistic regression will be used to assess the effects of treatment group on cessation outcomes and to test potential moderators.

**Discussion:**

This study will answer questions regarding the implementation and effectiveness of integrating a culturally specific video intervention into a real-world, population-level tobacco intervention. It will also aid our understanding of individual-difference variables that are associated with success. If an incremental benefit is found, this trial will have implications for increasing the responsiveness of tobacco quitlines for African Americans, reducing tobacco cessation disparities, and best practices for improving minority health. In addition, the *PTF* intervention has the potential for widespread disseminated through quitlines, which are available across the United States.

**Trial registration:**

Clinicaltrials.gov NCT03064971. Registered on February 22, 2017.

## Background

Racial disparities in tobacco control persist. African American adults are significantly more likely to report current smoking and have higher death rates from related illnesses relative to Whites [1]. This population is also less likely to achieve long-term tobacco use abstinence [2–4]. Multiple evidence-based interventions for cessation exist (e.g., face-to-face counseling), however their ability to provide cost-effective help on a mass scale is limited. Tobacco quitlines represent a population-based method of treatment delivery and serve more smokers per year than any other single-channel for moderate to intense counseling. Quitline counseling alone doubles the likelihood of cessation, and triples when combined with medication [5]. Quitlines are also important because they reduce barriers to care such as cost, health insurance, lack of transportation and/or childcare, and serve traditionally underserved populations, including ethnic/racial minorities and those living in rural settings [6].

Evidence suggests that African American smokers are interested in quitline services. Zhu et al. [7] found that compared to Whites, African American smokers are more likely to seek quitline services, and request counseling. Recent findings from the National American Quitline Consortium (NAQC) indicate that 18.7% of US quitlines callers self-identify as Black/African American which equals about 58,500 tobacco smokers each year [8], while being 13% of the U.S. population and 19% of smokers [1]. Few studies have reported outcomes by race/ethnicity, however, the extant literature demonstrates a lower likelihood of cessation among African American versus white quitline enrollees [9, 10]. It may be possible to enhance the efficacy of quitline services via culturally specific interventions, which integrate distinct social factors, such as history, beliefs, norms, smoking patterns, and cultural values and assets into the content. Culturally specific interventions are framed within a cultural context and are based on theory, empirical evidence, and characteristics of the target population [11, 12].

The literature suggests that culturally specific interventions are beneficial among some African American tobacco smokers. Research has found a general preference for culturally specific compared to standard interventions [13], and greater efficacy when delivered in a group intervention format [14]. However, given the heterogeneity within racial categories, the efficacy of culturally specific interventions may vary by individual differences [15]. The only published quitline study focused on African Americans found that culturally tailored counseling plus culturally specific written materials led to greater intervention satisfaction and quit attempts, yet effects on abstinence were less clear [16]. Given the disparity in cessation between African Americans and other racial groups, interventions with high scalability, and that reduce barriers to participation (e.g., accessibility, cost, health literacy, relevance), are needed. To this end, we developed and tested a video-based, culturally specific intervention designed for African American tobacco smokers, titled *“Pathways to Freedom: Leading the Way to a Smoke-Free Community”©(PTF)* [17].

The video-based *PTF* retains the framework of an earlier print-based *PTF* guide, which was guided by a model of community competence [18]. The video version is a substantial enhancement of the original guide, and translates the content of an efficacious cognitive behavioral therapy for smoking cessation adapted for African Americans [14]. The *PTF* video expands on topics such as the history of tobacco and African Americans, targeted tobacco industry marketing, mentholated cigarettes, the use of religion/spirituality as a coping strategy, and pharmacologic cessation aids. It utilizes cognitive behavioral strategies including cognitive restructuring and coping skill development, and highlights cultural assets. A 2-arm randomized trial demonstrated positive effects of *PTF* delivered as a digital video disc (DVD) compared to a standard control DVD [17]. Specifically, *PTF* was preferred and increased readiness to quit and risk perceptions.

### The present study

Despite the disparate tobacco use and illness rates, little attention has been placed on testing new behavioral approaches aimed at increasing quit rates among African American tobacco smokers. This randomized controlled trial (RCT) will seek to obtain real-world evidence for the efficacy of the *PTF* intervention as an enhancement to standard quitline counseling. The three aims of the study are to: (1) examine the effects of implementing a culturally specific, video-based intervention targeting African Americans in a state tobacco quitline; (2) examine the effect of *PTF* on treatment engagement; and (3) assess the feasibility of delivering *PTF* in an online format (exploratory). We hypothesize a positive effect of cultural specificity, such that the *PTF* intervention will demonstrate superior outcomes compared to the control conditions. The primary abstinence outcome will be cotinine-verified 7-day point-prevalence abstinence (ppa) at the 6-month follow-up. Secondary outcomes will include 7-day ppa at 3-months and treatment engagement. We will also examine ethno-cultural individual differences as moderating variables, including expectancies for culturally specific interventions, acculturation, and experiences of racial/ethnic discrimination.

## Methods/design

This study is a 3-arm semi-pragmatic randomized controlled trial (RCT) [19] that includes elements of both implementation and effectiveness research [20]. Pragmatically, recruitment, enrollment, and intervention delivery are occurring in a real-world setting (the quitline), and inclusion/exclusion criteria are minimal to increase access to care and study generalizability. Participants are randomly assigned to receive one of 3 interventions (Fig. 1): standard care plus *PTF* video, standard care plus standard smoking cessation video, or standard care only—all supplemented by 2-weeks of NRT (the standard supply offered through the quitline). To increase accessibility, participants in the video conditions are mailed a DVD and have access to a private YouTube channel for online viewing of their respective video. Assessments will occur at baseline, 3, and 6-months post-enrollment. Thus, the study will answer whether standard quitline counseling can be enhanced by the provision of a culturally specific video-based intervention.

**Fig. 1 Fig1:**
[figure not shown]
Study Design

### Participants

Participants are African American tobacco smokers recruited from the North Carolina State Quitline (QuitlineNC; *N* = 1050). Inclusion criteria include (1) self-identification as Black/African American; (2) current smokers (smoked at least 100 lifetime cigarettes and currently smoke on some or every day) who would like help quitting; (3) eligible for state quitline services; (4) over 18 years of age; (5) access to devices that play DVDs or the internet; and (6) permanent contact information. Exclusion criteria are: (1) recent quitters (have not smoked in the past 7 days), (2) planning to move within the next 6 months, and (3) not ready to set a quit date within 30 days.

### Randomization

The individual is the unit of randomization. The randomization scheme was developed using a computer-generated random numbers table. We are using stratified random sampling (by sex) with equal allocation to conditions. Randomization occurs through an automated algorithm after Quit Coaches® indicate within the computer system that a participant has provided verbal consent. Participants are blind to their intervention condition.

### Procedures

During initial quitline enrollment, callers who self-identify as Black/African American are screened for eligibility. Eligible enrollees are offered the opportunity to participate in the study, and those who agree are transferred to a research-trained quitline coach to provide verbal informed consent and complete the baseline measures. Participants are then randomized to a study condition, and then begin standard care services from the quitline (described below). Participants in the *PTF* or attention-control conditions will receive the assigned video in DVD format by mail, in addition to a text, email and/or mailed letter including the link to a private YouTube channel for online viewing. Monthly promotional items, and bi-weekly reminders serve as prompts to encourage use of the videos and/or utilize the quitline services. Incentives for assessment completion include $15 at baseline, $25 at the 3-month follow-up, $60 for the 6-month follow-up, and $20 for returned saliva samples. Participants can self-withdraw from the study by informing the study by telephone or in-writing.

#### Interventions

QuitlineNC is operated by Alere Wellbeing (owned by Optum), the leading provider of tobacco quitline services in the U.S. who delivers more than 350,000 coaching calls per year via 25 state quitlines and numerous commercial contracts. Beyond the initial counseling session, which occurs at baseline, participants may receive up to three additional proactive (i.e., Quit Coach initiated) counseling calls (Fig. 2), each designed to provide practical expert support to help participants develop problem-solving and coping skills, secure social support, and design a plan for successful cessation and long-term abstinence. Participants can also contact the quitline as needed for support between proactive calls. A 2-week “starter” pack of nicotine patches, which is consistent with standard quitline care, is provided at no-cost to participants per manufacturer dosing and usage instructions.

**Fig. 2 Fig2:**
[figure not shown]
Quit Coaching Call Schedule

##### Standard Quitline services (real-world control)

During the initial counseling session, Quit Coaches® work with participants to set a quit date and develop a personalized plan for quitting. Subsequent coaching calls focus on cessation-related challenges and/or the use of NRT. Quit Coaches® review and modify individualized quit plans, and provide support as appropriate. If participants have an unsuccessful quit attempt, Quit Coaches assist with planning a new quit date and/or resolving ambivalence. For individuals who have successfully quit, coaches focus on relapse prevention. Participants also receive standard self-help materials by mail, which is often referred to by Quit Coaches.

##### Standard Quitline services plus standard cessation video (attention-matched control)

This condition includes standard care provided by QuitlineNC, plus a standard smoking cessation video (DVD and online). The evidence-based “*How to Quit”* DVD [21] contains 60 min of smoking cessation information and strategies. It describes the process of quitting, and strategies for increasing physical activity and healthy nutrition. It includes testimonials from former smokers and dialogue among smokers in a group counseling setting. The information is presented in a standard format, intended for the general population of smokers. Quitline counselors are trained to refer participants to appropriate sections for additional help. This condition is included to control for attention effects.

##### Standard Quitline services plus PTF (PTF)

The experimental intervention will include the standard care provided by QuitlineNC, with the addition of *PTF* video (DVD or online). The content of the intervention parallels the types of education, advice, and cessation/relapse prevention strategies that are delivered in clinic and quitline contexts, except for the focus on the specific needs of the African American community. The 60-min video describes the history of tobacco and African Americans, the health consequences of tobacco use and second hand smoke, strategies for cessation and relapse prevention, and mobilizing the community to fight against the tobacco industry. The culturally specific elements (e.g., focus on targeted tobacco industry marketing, menthol tobacco products, concerns about pharmacotherapy, religion/spirituality, family and community, African American images and music, etc.) are infused throughout the video. Quit Coaches® are trained to refer participants to appropriate sections for additional help.

##### Online access

Participants in both video conditions will have the opportunity to view their assigned video via the Internet. The goal is to increase accessibility of the intervention and allow viewing on mobile devices. We will text, email (and mail) a link to participants allowing them to access their assigned video using a private YouTube channel. Participants will be able to select sections for viewing.

### Measures

#### Baseline (Table 1)

Standard quitline enrollment items include demographics, tobacco use history (age of initiation, current smoking, daily smoking, types of products used, history of quit attempts, prior use of quitline/telephone counseling services), time to first cigarette, health insurance, chronic medical conditions (e.g., asthma, cancer), stage of readiness to quit, and electronic cigarette use. Study-specific measures include readiness to quit [22], perceived stress [23], depressive symptoms [24], acculturation [25], ethnic identity [26], ethnic discrimination scale [27], culturally specific intervention expectancy, and social support [28]. Measures are minimized to reduce participant burden.

**Table 1 Tab1:** Study Specific Data Collection

Measure	Baseline	3-Month Follow-Up	6-Month Follow-Up
Demographics	X		
Tobacco Use	X		
Weight concerns	X		
Readiness to Quit	X	X	X
Perceived Stress	X	X	X
Depressive Symptoms	X	X	X
Acculturation	X		
Ethnic Identity	X		
Expectancies for Culturally Specific Interventions	X		
Perceived Social Support	X	X	X
Perceived Ethnic Discrimination	X		
Treatment Engagement		X	X
Treatment Utilization		X	X
TNP Use		X	X
Intervention Ratings		X	
Time-Line Follow-Back (smoking pattern)		X	X
Cotinine^a^			X

^a^Saliva for cotinine analysis is collected from self-reported abstainers only

#### Follow-up (3, and 6-months, Table 1)

Assessments are completed via telephone approximately 3 and 6-months after study enrollment (Fig. 1). Measures include treatment engagement [29], number of coaching calls completed, intervention ratings [17], readiness to quit [22], perceived stress [23], depressive symptoms [24], social support [28], and video utilization (number of time watched DVDs and online viewing). The time-line follow-back (TLFB) [30, 31] assesses 7-day ppa, pharmacotherapy use. Participants who report 7-day ppa at the 6-month follow-up are sent a saliva collection kit to confirm abstinence via cotinine, which includes a prepaid postage envelope. Seven ng/ml distinguishes smokers from nonsmokers [32]. Those not returning saliva are considered smokers.

### Data analyses

#### Sample size and power

Previous research found 10–29% quit rates among African American quitline callers [9]. Our preliminary research showed a 7% difference in self-reported verified cessation, between participants who received only the *PTF* DVD vs. the Standard control (no additional counseling or NRT). Using the formula provided in Diggle et al. [33] (p. 31), we anticipated a 7% difference in 7-day ppa at 6-months between the *PTF* (32%) vs. control (25%) conditions, with a power of .80, alpha of .05, which requires 350 participants/condition.

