#### Statistical analysis

Preliminary analyses will include descriptive statistics, analyses of variance and chi-square tests to examine group differences in baseline variables. If any differences are found, these variables will be entered as covariates in outcome analyses. Pattern mixture analyses will examine selection bias by comparing the characteristics and outcomes of participants who completed the study to those who did not both across and within study groups. Alpha will be set to .05, and adjusted for multiple comparisons if needed. Missing values are expected, and will be handled using methods such as multiple imputation, maximum likelihood estimation, and intent-to-treat analyses. The primary outcome is biochemically verified 7-day ppa (1 = cessation, 0 = smoking) at 6-months. Generalized linear mixed models (GLMMs) will test the longitudinal effect of intervention condition on abstinence, including interaction terms and adjusting for covariates. Controlling for covariates, hierarchical logistic regressions will determine the odds of abstinence at the 3-month follow-up (secondary outcome), and treatment engagement and potential moderating variables (e.g., acculturation, ethnic identify, readiness to quit) will be analyzed with analyses of covariance and hierarchical regression analyses.

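### The power statement does not establish that 32% vs 25% are rates of the cotinine-verified primary outcome, and 350 per arm gives about 54% power rather than 80% even with no loss at verification

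*Protocol article*

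**What the plan says.** All references are to the protocol article.

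- **Sample size and power, background rate.** "Previous research found 10–29% quit rates among African American quitline callers". Whether these rates were verified is not said.
- **Sample size and power, source of the effect.** "Our preliminary research showed a 7% difference in self-reported verified cessation", comparing the PTF DVD with the standard control DVD, without counseling or NRT.
- **Sample size and power, planning target.** "we anticipated a 7% difference in 7-day ppa at 6-months between the" PTF and control conditions, the rates being given as "32%) vs. control (25%) conditions", "with a power of .80, alpha of .05", "which requires 350 participants/condition". The target is not called verified, and no allowance for verification is mentioned.
- **Statistical analysis.** "The primary outcome is biochemically verified 7-day ppa" at 6 months. The Abstract and the section on the present study also call the primary outcome biochemically or cotinine verified.
- **Follow-up.** Participants who report 7-day ppa at 6 months are mailed a saliva kit with a 7 ng/ml cut-off, and "Those not returning saliva are considered smokers". Here 7-day ppa, unqualified, means the self-report that triggers the kit.
- **Table 1.** Cotinine is measured at 6 months only, and only in self-reported abstainers.

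**The concern.** Under the follow-up rules, a participant who reports abstinence counts as a success only if the kit comes back and the sample passes the cut-off. The verified rate can therefore only equal or fall below the self-reported rate. The planning rates should be on the scale that will be analysed, and the article does not show that they are. The planning sentence omits the qualifier that the article uses elsewhere for the primary outcome. The source sentence applies both labels at once.

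The planning figure is what readers will use to interpret a null result. If the 7 points and the 80% do not belong to the verified 6-month comparison, a non-significant result would be read as stronger evidence against a 7-point benefit than the trial can supply.

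**Working it through.** **Inputs.** Rates 32% and 25%, power .80, alpha .05 and 350 per condition come from the sample-size section; equal allocation comes from the randomization section. The article does not state sidedness, so two-sided is assumed. It gives no share of self-reported quitters who will be verified, so a range is used.

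**Step 1: the plan's own figure.** For two proportions with pooled variance under the null,

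n per arm = [1.960·√(2p̄(1−p̄)) + 0.842·√(p₁(1−p₁) + p₂(1−p₂))]² / (p₁−p₂)²

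With p₁ = .32, p₂ = .25 and p̄ = .285, the two roots are √.40755 = .6384 and √.4051 = .6365. This gives n = 651.6, so 652 per arm.

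Other versions do not give 350 either:
- two-sided: 680 with continuity correction, 649 unpooled, 651 arcsine
- one-sided: 514, or 542 with continuity correction

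The stated 350 is not reproduced for a single 6-month comparison.

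**Step 2: power at 350 per arm with no verification loss.**

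Power = Φ{[(p₁−p₂)√n − 1.960·√(2p̄(1−p̄))] / √(p₁(1−p₁) + p₂(1−p₂))}

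= Φ{(1.3096 − 1.960 × .6384) / .6365} = Φ(0.09) = 53.7%

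One-sided it is 66%. This is the baseline against which any effect of verification must be judged.

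**Step 3: if 32% and 25% are self-reported.** Let a share f of self-reported abstainers return a kit and pass, equal in both arms. The rates become .32f and .25f, and the difference becomes .07f. Two-sided, 350 per arm:

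| f | PTF vs control | Power | Loss from 53.7% | n per arm for 80% |
|---|---|---|---|---|
| 1.0 | 32.0% vs 25.0% | 53.7% | none | 652 |
| 0.9 | 28.8% vs 22.5% | 47.9% | 5.7 points | 754 |
| 0.8 | 25.6% vs 20.0% | 42.3% | 11.4 points | 880 |
| 0.7 | 22.4% vs 17.5% | 36.7% | 16.9 points | 1043 |
| 0.6 | 19.2% vs 15.0% | 31.4% | 22.3 points | 1261 |
| 0.5 | 16.0% vs 12.5% | 26.2% | 27.4 points | 1565 |

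Losses are taken from unrounded values. The part due to verification is thus about 6 to 27 points. The rest of the gap to 80% is the arithmetic problem of steps 1 and 2.

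**Step 4: if a full 7 points holds on the verified scale at a lower control rate.** Same formula, 350 per arm:

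| PTF vs control | Power | n per arm for 80% |
|---|---|---|
| 27% vs 20% | 59% | 575 |
| 22% vs 15% | 67% | 482 |
| 17% vs 10% | 77% | 373 |

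This is more favourable than step 2, but it assumes a larger relative effect: 17/10 = 1.70-fold in the last row, against 32/25 = 1.28-fold as planned.

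**The case against.** The strongest reply is that a reader might infer that the trial was powered for a different and easier endpoint, and that the article does not show this. That reply stands:

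- The source sentence contains the word verified, and could be read as self-reports that were then verified.
- The planning sentence names the same measure and time point as the primary outcome, so the short label may stand for the verified rate. The follow-up section uses that label for the self-report, so the text supports both readings.
- A lower verified rate does not always cost power. Power falls if the difference shrinks in proportion to the rates (step 3). It rises if 7 points is kept (step 4).
- The position of the planning rates shows nothing about scale. The control rate of 25% lies inside the cited 10–29%. A PTF rate above that range is what the trial hypothesises.
- Loss to follow-up should not be folded into the verified share. Those who report abstinence at 6 months have already been reached, the smoking rule in the follow-up section covers unreturned saliva, and other missing values are assigned to multiple imputation, likelihood and intent-to-treat methods.

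It can also be said that the cited textbook formula may average over repeated measurements. Assuming a factor (1+(m−1)ρ)/m applied to 652, two measurements give 350 at ρ of about 0.07, and three at about 0.31. The article states neither m nor ρ. Such a figure would not be the power of a single 6-month comparison, and cotinine is collected once, so the verified outcome has no repeat to average over. Comparing PTF with both controls pooled (350 vs 700) does not rescue the claim either: 67% two-sided, 77% one-sided.

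Finally, a condensed article may leave attrition detail to the full protocol. But this article prints a specific justification, and its source label and target do not match the primary outcome it states. That is a printed item fixed badly rather than a detail left out.

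**Conclusion.** The concern holds as a failure to establish the scale, not as proof that the wrong endpoint was used. The article does not show that 32% and 25% are rates of verified abstinence, the label on the pilot effect contradicts itself, and no verification loss is allowed for.

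For a two-sided .05 comparison at 6 months with 350 per arm, none of the scenarios computed reaches 80%. Power is about 54% with the rates as printed, 48% down to 26% if they are self-reported and 90% down to 50% are verified equally in both arms, and 59% to 77% if 7 points is assumed on the verified scale from control rates of 20% down to 10%. These figures rest on the two-sided test, the assumed verified shares and, in the proportional case, equal shares in both arms. The article confirms none of these.

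**What to change.** In the sample-size section:

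1. State whether the preliminary 7-point difference was self-reported or verified, and the same for the 32% and 25%.
2. Give the planning rates on the verified scale, with the assumed kit-return and confirmation share behind them.
3. Replace the single 80% claim with power at 350 per arm over that range, as in the tables above, stating sidedness. If a repeated-measures formula was used, give the number of measurements and the correlation, and keep that figure separate from the 6-month verified comparison.

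Reporting self-reported 6-month abstinence as a secondary outcome would let the planned effect be examined on that scale, but this is a preference and not part of the correction.

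The cost is a few sentences and a short table. No participants or data are added. The downside is that the stated power becomes less favourable.

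### For 32% vs 25% abstinence at 6 months, 350 per arm gives about 54% power two-sided (66% one-sided), not the stated 80%

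*Protocol article*

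**What the plan says.** The Sample size and power section anticipates a "7% difference in 7-day ppa at 6-months between the *PTF* (32%) vs. control (25%) conditions" and continues "with a power of .80, alpha of .05, which requires 350 participants/condition". It attributes the number to a formula in a cited reference. The article does not reproduce that formula, and it gives no number of visits, no within-person correlation and no sidedness.

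The endpoint is fixed elsewhere. The Statistical analysis section states: "The primary outcome is biochemically verified 7-day ppa", at 6 months, coded as a binary outcome. The Abstract and The present study say the same, and The present study lists 3-month abstinence as a secondary outcome. Table 1 schedules cotinine at 6 months only, with the footnote "Saliva for cotinine analysis is collected from self-reported abstainers only". The Follow-up section counts people who do not return saliva as smokers.

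The total is 1050 in three arms, using "stratified random sampling (by sex) with equal allocation to conditions", which is 350 per arm. On error rate, the Statistical analysis section says: "Alpha will be set to .05, and adjusted for multiple comparisons if needed".

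**The concern.** The sample-size statement gives everything needed to check it except the sidedness: two proportions, a time point, a power, an alpha and a number per arm. A 7-point difference near 25–30% usually needs well over 500 per arm for 80% power, so 350 looked too small whichever way the test is run.

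What is at stake is how the result will be read. A reader who trusts 80% power may take a non-significant result as fair evidence that the video adds less than 7 points. The Discussion links a positive result to dissemination through all 50 state quitlines, so the negative reading matters equally.

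**Working it through.** **Inputs (protocol article).** p1 = .32, p2 = .25, difference d = .07, power .80 (z = 0.8416), alpha .05 and 350 per arm, all from Sample size and power. Equal allocation comes from Randomization. Sidedness is not given, so both cases are shown: z = 1.9600 two-sided, z = 1.6449 one-sided.

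**Step 1. Try to reproduce 350.** The pooled-variance formula for two proportions is

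n = [z_alpha × √(2·p̄·q̄) + z_power × √(p1q1 + p2q2)]² / d²

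with p̄ = .285, so 2 × .285 × .715 = .40755 (root .6384), and .32 × .68 + .25 × .75 = .4051 (root .6365).

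- Two-sided: (1.9600 × .6384 + 0.8416 × .6365)² / .0049 = (1.7869)² / .0049 = 651.6, so 652 per arm.
- One-sided: (1.6449 × .6384 + 0.8416 × .6365)² / .0049 = (1.5857)² / .0049 = 513.2, so 514 per arm.

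| Variant | Two-sided | One-sided |
|---|---|---|
| Pooled variance | 652 | 514 |
| Unpooled variance | 649 | 512 |
| Arcsine | 651 | 513 |
| Continuity-corrected | 680 | 542 |

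No variant comes near 350.

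**Step 2. Power at 350 per arm.** Power = Φ[(d√n − z_alpha × .6384) / .6365], with d√n = .07 × √350 = 1.3096.

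- Two-sided: (1.3096 − 1.2512) / .6365 = 0.092, giving 53.7%.
- One-sided: (1.3096 − 1.0501) / .6365 = 0.408, giving 65.8%.

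A simulation of 400,000 trials gave 53.6% and 66.0%. The chance of missing a true 7-point benefit is therefore 1 − .537 = 46% two-sided and 1 − .658 = 34% one-sided.

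**Step 3. Pool the two controls.** For 350 vs 700, the same method gives 66.6% two-sided and 77.0% one-sided.

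**Step 4. Split alpha over two control comparisons.** At two-sided .025, 350 vs 350 gives 42.4%. The article leaves this adjustment open, so this is a what-if.

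**Step 5. Could repeated measures explain 350?** Averaging m equally correlated visits multiplies n by (1 + (m − 1)ρ)/m. Setting the result to 350 and solving for ρ:

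- m = 2: two-sided, 2 × 350/651.6 − 1 = 0.07; one-sided, 2 × 350/513.2 − 1 = 0.36.
- m = 3: two-sided, (3 × 350/651.6 − 1)/2 = 0.31; one-sided, (3 × 350/513.2 − 1)/2 = 0.52.

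The trial has two follow-ups, so two visits, one-sided, with ρ about 0.36 is a natural reconstruction. It is an inference, because the article states none of these inputs.

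**Step 6. What 350 per arm does support.** With control at 25%, 80% power is reached at about 34.7% two-sided (9.7 points), or about 33.5% one-sided (8.5 points). The 95% CI half-width at the planned rates is 1.96 × √(.4051/350) = .067, or 6.7 points. An observed difference above about 7.0 − 6.7 = 0.3 points would therefore leave 7 points inside the interval.

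**The case against.** The best defence is that the plan is longitudinal. The Statistical analysis section specifies generalized linear mixed models for the effect over time, the time-line follow-back assesses 7-day abstinence at both 3 and 6 months, and the sample-size sentence does not use the word verified. A two-visit abstinence outcome does exist, so a reader who infers that the trial has nothing to average over would be wrong.

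That much stands, but it does not restore the 80%. The sample-size sentence ties the 7-point difference to 6 months. A model with a group-by-time interaction estimates the 6-month contrast essentially from 6-month data. A model without it estimates an average of 3 and 6 months, mixing unverified with verified abstinence. That is a different quantity from the primary outcome, and 3-month abstinence is listed as a separate secondary outcome.

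A second defence is condensation: the visits, correlation and sidedness may be in the full protocol. Their absence from the article is accepted and is not the point. The mismatch is among figures that the article itself prints.

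A third is that other control rates are more favourable. The article cites quit rates of 10–29%. For a 7-point difference at 350 per arm, two-sided power runs from 77.5% (control 10%) down to 50.7% (control 29%), so it stays below 80%. One-sided, it reaches 85.8% at a 10% control rate, so one cannot say that 80% is out of reach throughout that range. The planned control rate, however, is 25%.

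**Conclusion.** The power statement is wrong as written. For the stated 6-month contrast, 350 per arm is 54% of the two-sided requirement (350/652) and 68% of the one-sided requirement (350/514). Power is about 54% or 66%, and neither sidedness nor pooling the controls brings it to 80%.

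This rests on a single two-arm comparison at 6 months, alpha .05 without multiplicity adjustment, all 350 per arm analysed, and true rates of 32% and 25% after unreturned saliva is counted as smoking.

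Two stronger readings are not supported. A reader might infer that a null result is likely even if the planned effect is real. At 46% (two-sided) or 34% (one-sided), a non-significant result is the less likely outcome, though two-sided it is close to a coin flip. A reader might also infer that a repeated-measures formula was certainly misapplied. The article does not show how 350 was obtained, and the finding does not depend on it.

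**What to change.** Keep N = 1050 and revise the Sample size and power section to:

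- state whether the test is one- or two-sided;
- give power for the 6-month contrast of 32% vs 25% at 350 per arm as about 54% two-sided (about 66% if one-sided);
- give the difference detectable with 80% power as about 9.7 points two-sided (25% vs 34.7%), or about 8.5 points one-sided;
- credit no repeated-measures gain to this endpoint. If power for an effect averaged over 3 and 6 months is also of interest, report it separately with the number of visits and the correlation;
- add that, with a 95% CI half-width of about 6.7 points, a non-significant result may not exclude a 7-point benefit.

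The cost is a few sentences and a less favourable stated power. No extra participants and no change to design or analysis are needed. Reaching 80% power for 7 points would instead take 3 × 652 = 1956 participants two-sided or 3 × 514 = 1542 one-sided, which is not proposed here.
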